#### Efficacy outcomes

Refracted ETDRS BCVA at 6 months (mean change in ETDRS letter score from baseline).Surgical success (proportion with FTMH closure within 3 months without further FTMH surgery).Area under the BCVA versus time curve (ETDRS letter score).

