### Sample size

For feasibility and pilot studies, sample sizes between 24 and 50 have been recommended to estimate a chosen parameter.^31 32^ Using a 1:1 treatment to control ratio, a total sample size of 60 would be sufficient to estimate the SD of the outcome of at least 28 treated participants per group, with 7% attrition. We aim to estimate the screening success (assumed as 70%; 95% CI 60% to 80%) from approximately 105 potentially eligible participants.

Of the 60 participants, we will enrol at least 16 with small FTMHs (<250 µm minimum linear diameter), 16 medium (250–400 µm) and 16 large (>400 µm). We feel it is appropriate to recruit holes of varying size. This will support generalisability and provide the evidence needed to inform a future study design.

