### Assignment of interventions

Participants will be randomised at the time of screening once the investigator has confirmed eligibility, and a decision has been made regarding combined surgery.

Participants will undergo randomisation by the process of minimisation, prior to surgery in a ratio of 1:1. They will be stratified based on planned operation (combined procedure or FTMH surgery alone) and FTMH size (small, medium and large). Phacoemulsification and IOL implant can be performed prior to vitrectomy in a ‘combined procedure’ if deemed appropriate, but the decision to undertake phacoemulsification should be made prior to randomisation.

A web-based bespoke randomisation system has been created in collaboration with the trial statisticians and the chief investigator (CI) and maintained by the KCTU for the duration of the project. It will be hosted on a dedicated server within King’s College London.

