### Statistical methods

#### Statistical methods for primary and secondary outcomes

The proportion of patients who are successfully recruited after screening will be reported with 95% CIs computed by the exact binomial method, as will all outcomes assessing feasibility except for recruitment rate, which will be reported per site per month. In addition to summary statistics of the secondary outcomes (similarly to the primary and baseline outcomes), all harms and withdrawals will be reported with 95% CIs.

An exploratory efficacy analysis will be based on intent-to-treat and include all randomised participants. A secondary analysis will be per protocol comparing those who had gasless vs standard surgery, irrespective of allocation, to investigate the effect of cross-over. The safety population will include all participants who underwent randomisation.

The proportion of participants with primary surgical anatomical closure and mean BCVA (change from baseline, and area under the curve (AUC)) will be compared between groups at 6 months (Fisher’s exact test and Mann-Whitney, respectively). For the AUC analysis, VA will often be below 1 ETDRS letter when gas is in the eye, so ETDRS acuity will be converted to logarithm of the minimum angle of resolution (logMAR) with assignment of logMAR values to count fingers or worse^36^:

Count fingers at 2 ft: logMAR+1.85.

Hand motions at 2 ft: logMAR+2.3.

Visual acuity of ‘light perception’ or ‘no light perception’ will not be converted and will be reported separately.

Adherence to posturing and treatment acceptability will be described.

The MacTSQ has been validated for use in macular diseases requiring drug administration and consists of two subscales: information provision/convenience and treatment satisfaction.^35^ The individual scores from each subscale as well as the composite score will be analysed based on change from the first time point (paired sample t-test) and between groups (analysis of variance model).

Quantifiable findings from the MacTSQ will be analysed using descriptive statistics. Open-ended responses will be analysed for descriptive and analytic accounts using thematic analysis and a constant comparison approach. Analysis will pay particular attention to key factors that impact on patient experiences both positively and negatively and will integrate quantifiable data from the MacTSQ in the analysis to investigate patterns of experience within the participant population.

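### The main efficacy comparison is two unadjusted tests, with no stated between-group estimate or CI; for BCVA the rank test does not match the mean change defined as the outcome

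*Protocol article*

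**What the plan says.** All references are to the protocol article; the separate SAP it mentions is not available.

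- **Outcomes.** Efficacy outcomes defines the acuity outcome as "Refracted ETDRS BCVA at 6 months (mean change in ETDRS letter score from baseline" and surgical success as "proportion with FTMH closure within 3 months without further FTMH surgery".
- **Comparison.** Statistical methods for primary and secondary outcomes says that closure and "mean BCVA (change from baseline, and area under the curve (AUC)) will be compared between groups at 6 months", using Fisher's "exact test and Mann-Whitney, respectively". No covariate is named. The same section attaches 95% CIs to the feasibility outcomes (except recruitment rate), harms and withdrawals. It plans summary statistics for secondary outcomes and calls the efficacy analysis exploratory.
- **Allocation.** Assignment of interventions says: "Participants will undergo randomisation by the process of minimisation, prior to surgery in a ratio of 1:1". The factors are given as "stratified based on planned operation (combined procedure or FTMH surgery alone) and FTMH size (small, medium and large").
- **Subgroups.** Methods for additional analyses lists operation performed and hole size among the exploratory subgroup factors, to be applied as effects to the efficacy outcomes. It says that hole size affects closure and that combined cataract surgery may affect acuity.
- **Purpose.** Objectives gives preliminary efficacy data and the design of a future trial as aims. Sample size rests on being able to "estimate the SD of the outcome of at least 28 treated participants per group, with 7% attrition".

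**The concern.** The stated method does not match the stated outcome and purpose in three ways.

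1. The outcome is a mean change in letters. A Mann-Whitney test compares rank distributions. It neither tests nor estimates a difference in means, so it does not deliver the quantity a pivotal trial would be designed around.
2. Subtracting baseline is not the same as adjusting for it. A change score uses baseline with a fixed coefficient of 1, whereas ANCOVA estimates the coefficient and is at least as precise in large samples. Hole size and planned operation are balanced by the allocation and then left out of the main comparison, so that comparison gains no precision from the balance.
3. For closure, a p-value from about 28 to 30 patients per arm at high closure rates says very little. A non-significant result could be read as similarity when a clinically large loss of closure has not been excluded.

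At stake is the usefulness of the efficacy data for planning the next trial: a difference, its interval, and the residual SD.

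**Working it through.** **The plan's own figure.** 56 evaluable patients (28 per arm) with 7% attrition: 56/0.93 = 60.2, which rounds up to 61, and 60 × 0.93 = 55.8, about 28 per arm. The stated 60 is reproduced to within rounding. It rests on estimating an SD and does not depend on the choice of test.

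**BCVA: change score against ANCOVA.** The article gives no SD and no baseline-to-6-month correlation r, so r is assumed. Baseline and 6-month variances are taken as equal and set to 1.

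- Variance of a change score: 2(1 − r).
- Residual variance under ANCOVA: 1 − r².
- Ratio: (1 − r²)/(2(1 − r)) = (1 + r)/2.
- 95% CI half-width at 28 per arm, in outcome SDs: 1.96 × √(variance × 2/28).

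| assumed r | change variance | ANCOVA variance | ratio | half-width, change | half-width, ANCOVA | per arm for change score to match 28 with ANCOVA |
|---|---|---|---|---|---|---|
| 0.3 | 1.40 | 0.91 | 0.65 | 0.62 | 0.50 | 43.1 |
| 0.5 | 1.00 | 0.75 | 0.75 | 0.52 | 0.45 | 37.3 |
| 0.7 | 0.60 | 0.51 | 0.85 | 0.41 | 0.37 | 32.9 |

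The last column is 28 divided by the ratio. The benchmark is a mean-based analysis of change, not the Mann-Whitney test itself, so the table shows what covariate adjustment adds and not the exact loss from the rank test.

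**Leaving out the minimisation factors.** Unadjusted Mann-Whitney was simulated with no treatment effect, 60 patients and allocation balanced within six strata of 10 (an approximation to minimisation), at nominal two-sided 0.05. The share of outcome variance explained by the strata (R²) is assumed.

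| R² of strata | actual type I error |
|---|---|
| 0 | 0.045 |
| 0.1 | 0.035 |
| 0.2 | 0.025 |
| 0.3 | 0.020 |
| 0.4 | 0.013 |

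The error falls below nominal; it does not rise.

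**Closure: what Fisher's test conveys.** Alpha (two-sided 0.05) and the closure rates are assumed. For orientation, the Background reports 91.7% to 100% in five earlier gasless series and 80% in the sixth. Exact enumeration gives:

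| true closure | rejection probability, 28 per arm | 30 per arm |
|---|---|---|
| 90% v 90% (type I error) | 0.8% | 0.9% |
| 95% v 85% | 7.8% | 9.3% |
| 95% v 80% | 21% | 24% |

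Now take an illustrative result of 27/30 v 28/30.

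- Fisher p = 1.00.
- Difference: 0.900 − 0.933 = −0.033.
- Wilson 95% limits: 0.744 to 0.965 for 27/30, and 0.787 to 0.982 for 28/30.
- Newcombe lower limit: −0.033 − √((0.900 − 0.744)² + (0.982 − 0.933)²) = −0.197.
- Newcombe upper limit: −0.033 + √((0.965 − 0.900)² + (0.933 − 0.787)²) = +0.127.

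The interval is −20 to +13 percentage points. The p-value alone does not show that a loss of 20 points is still compatible with the data.

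**The case against.** The strongest reply is that this is a condensed article and a detailed SAP exists. Estimates, intervals and covariates may be there, and silence in the article does not exclude them. That is fair, so the point is not that the SAP lacks them. It is that the article does fix a method for the main comparison, and the method it fixes is unadjusted and, for BCVA, rank-based.

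Four stronger readings are tempting, and the documents do not support them.

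- **That the two tests are the whole efficacy analysis.** Group summary statistics are planned, and crude differences can be derived from them. The per-group SD is the sample-size rationale, so only the covariate-adjusted SD goes unmentioned.
- **That baseline BCVA is ignored.** It enters the change score by subtraction. Only the AUC has no stated baseline handling.
- **That the minimisation factors are ignored.** Closely matching factors are applied as effects in the prespecified subgroup analyses. Those are exploratory, however, and use the operation performed instead of the one planned, so they do not replace adjustment in the main comparison.
- **That the tests cannot give an effect size.** Fisher's test has a companion odds ratio with an exact interval, and Mann-Whitney has the Hodges-Lehmann shift. The article names neither.

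Two further objections stand. Low power of Fisher's test is no fault in itself, because efficacy is exploratory and no power is claimed. For AUC a rank test is defensible: fixed logMAR values are assigned to count fingers and hand motions, and light perception or worse is left unconverted, so values may clump in the gas arm and means would depend on the assignments.

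**Conclusion.** The point holds as a worthwhile improvement to a stated method, not as a flaw that invalidates the analysis. The named BCVA test does not estimate the mean change that defines the outcome. Baseline acuity and the minimisation factors are not covariates in the main comparison, and the article states no efficacy difference with a confidence interval.

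The consequence is lost precision and p-values that are conservative and say little. Nothing here shows bias or an inflated type I error. With equal variances and assumed r of 0.3 to 0.7, a mean change-score analysis carries 15% to 35% less information than baseline-adjusted ANCOVA. The correlation, the variance explained by the strata, alpha and the closure counts are all assumptions, because the article gives none of them; the direction of the result does not depend on their exact values.

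**What to change.** - **6-month BCVA:** make ANCOVA the main analysis, with baseline BCVA, planned operation and hole-size category as covariates. Report the adjusted mean letter difference with its 95% CI and the residual SD. Keep Mann-Whitney as a sensitivity check.
- **Closure:** report the risk difference with a Newcombe or Miettinen-Nurminen 95% CI alongside Fisher's test. Covariate adjustment need not be required, because non-closures will probably be few.
- **AUC:** keep the rank test and add a between-group difference with 95% CI, for example Hodges-Lehmann. A baseline-adjusted model can support it.

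If the SAP already specifies these, align the article's description with it.

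The cost is slightly more analysis work and, for BCVA, reliance on a linear model, which the retained rank test covers. Baseline acuity, hole size and planned operation are already recorded before randomisation, so sample size, visits and patient burden stay the same.

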### Who will be blinded?

BCVA and central optical coherence tomography (OCT) assessors will be masked to study treatment allocation. Due to the presence of gas within the eye, it is not possible to mask participants, and while still in the eye, it is also not possible to mask BCVA assessors. Hence, the BCVA assessments on day 1, day 7 and month 1 will be performed by an unmasked assessor, as the gas will probably be present at these visits. The assessment of OCT images at a site level is not masked, but a masked grader will assess OCT images sent to an independent reading centre, to determine the OCT-based efficacy outcome measure (anatomic closure).

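### The acuity AUC gives no value to light perception or no light perception, so an eye with worse vision can score better, most likely in the gas arm

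*Protocol article*

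**What the plan says.** The section on statistical methods for primary and secondary outcomes in the protocol article explains why the AUC is computed in logMAR: "VA will often be below 1 ETDRS letter when gas is in the eye". It announces values for count fingers or worse and gives two: "Count fingers at 2 ft: logMAR+1.85" and "Hand motions at 2 ft: logMAR+2.3". Light perception and no light perception, by contrast, "will not be converted and will be reported separately".

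The same section says the exploratory efficacy analysis is "based on intent-to-treat and include all randomised participants". Closure is compared by Fisher's exact test, and acuity change and AUC by Mann-Whitney ("Fisher’s exact test and Mann-Whitney, respectively").

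The AUC is one of three outcomes under Efficacy outcomes, where its scale is given as the ETDRS letter score. The section on blinding has acuity at day 1, day 7 and month 1 taken by an unmasked assessor, "as the gas will probably be present at these visits". Under Intervention, gas is part of the standard operation. The gasless arm receives it only if the hole cannot be occluded or to deal with a complication.

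**The concern.** This is a stated rule, not a detail left to the statistical analysis plan: an LP or NLP reading has no number to enter the AUC. Whether a reading is left out depends on the outcome itself, because only the worst readings go. It very probably depends on the arm too, because eyes holding gas are the ones expected to have very poor early vision.

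Without a value, two routes are open, and each has a cost:

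- **Skip the visit and interpolate.** The gap is bridged by better readings on either side, so a worse eye can receive a better score and be ranked on the wrong side of a less impaired one.
- **Drop the participant.** The analysis set then loses people because of a poor result, contrary to the intention to include all randomised participants.

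The AUC is the only listed efficacy outcome that uses the early visits for acuity, and the trial's data are meant to inform a pivotal trial. A systematic error in the estimate therefore matters even where a test would still reject.

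**Working it through.** **Plan's own figures.** The article gives no figure for the AUC. The one design figure used below is group size: 60 × (1 − 0.07) / 2 = 27.9, which reproduces the stated 28 per group.

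**Inputs from the article.** Visits at day 1, week 1 and months 1, 3 and 6; count fingers 1.85; hand motions 2.3.

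**Assumptions.** Visits at days 0, 1, 7, 30, 91 and 182; screening acuity placed at day 0; one letter = 0.02 logMAR, so a logMAR difference × 50 gives letters; LP, where scored, between 2.5 and 3.0. All acuity paths and LP rates are assumed.

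**Formula.** AUC = Σ (yᵢ + yᵢ₊₁)/2 × (tᵢ₊₁ − tᵢ); mean logMAR = AUC / 182. Higher is worse.

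**One gas-arm eye.** Baseline 0.7, then 1.0, 0.5 and 0.4 at months 1, 3 and 6. Days 30 to 182 contribute 0.75 × 61 + 0.45 × 91 = 45.75 + 40.95 = 86.70 in every row.

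| Day 1 and week 1 | Days 0 to 30 | AUC | Mean logMAR |
|---|---|---|---|
| Count fingers at both | 1.275 + 11.1 + 32.775 | 131.85 | 0.724 |
| Hand motions at both | 1.5 + 13.8 + 37.95 | 139.95 | 0.769 |
| LP at both, scored 2.5 | 1.6 + 15.0 + 40.25 | 143.55 | 0.789 |
| LP at both, scored 3.0 | 1.85 + 18.0 + 46.0 | 152.55 | 0.838 |
| LP at both, skipped | 0.85 × 30 = 25.5 | 112.20 | 0.616 |

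The skipped-LP eye (0.616) scores better than the same eye with count fingers (0.724) or hand motions (0.769). Its error is (143.55 − 112.20)/182 × 50 = 8.6 letters with LP at 2.5, and (152.55 − 112.20)/182 × 50 = 11.1 letters with LP at 3.0.

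**LP at day 1 only, hand motions at week 1.** Skipped: 10.5 + 37.95 + 86.70 = 135.15. Scored 2.5: 1.6 + 14.4 + 37.95 + 86.70 = 140.65. Scored 3.0: 1.85 + 15.9 + 37.95 + 86.70 = 142.40. The error is 5.50/182 × 50 = 1.5 letters to 7.25/182 × 50 = 2.0 letters.

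**Difference between arms.** Assumed mean paths: gas 0.8, 2.3, 2.3, 1.0, 0.5, 0.4; gasless 0.8, 0.8, 0.7, 0.6, 0.45, 0.4. Their AUCs are 140.0 and 90.95, a difference of 49.05 logMAR-days. Take LP = 2.7, a share p of the gas arm with LP at day 1, half of these also at week 1, and no LP in the gasless arm. The AUC with LP scored is 141.4 (day 1 only) or 147.2 (both visits). With LP skipped it is 135.5 or 113.7, so the losses are 5.9 and 33.5. Then

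shrinkage = p × (5.9 + 33.5)/2 ÷ [49.05 + p × (1.4 + 7.2)/2] = 19.7p ÷ (49.05 + 4.3p).

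- p = 5%: 0.985 / 49.27 = 2.0%
- p = 10%: 1.97 / 49.48 = 4.0%
- p = 20%: 3.94 / 49.91 = 7.9%
- p = 100%: 19.7 / 53.35 = 36.9%

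A simulation of the same setting (28 per arm, 300 runs per rate, with between-person and visit variation) gave 1.9%, 4.2%, 7.3% and 36.8%, in agreement within simulation error. Mann-Whitney on the AUC with LP skipped still rejected in at least 90% of runs at every rate. Dropping affected participants shrank the mean difference by only about 0.5% to 4% for p from 5% to 60%, but removed that share of the gas arm.

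**The case against.** The strongest reply is that the loss is partial and disclosed. Count fingers and hand motions stay in the AUC at poor values, and LP and NLP are reported separately. The conversion to logMAR was introduced because gas-filled eyes see so little. All of that stands. A reader might infer that the rule hides the early visual cost of gas. The article does not support that: the cost is attenuated, and in the assumed setting the test still detected it in most runs. A separate listing does not, however, correct the AUC or its ranks.

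A reader might also infer that an eye losing all sight would disappear from the efficacy results. That is not supported either. The non-conversion rule belongs to the AUC. Six-month acuity change is a separate outcome, no text excludes such eyes from it, and the loss would also fall under adverse events and complications.

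Third, the article states no LP or NLP frequency. Acuity below one letter includes count fingers and hand motions, both of which are converted. That LP falls mainly on the gas arm is a sound inference from who receives gas, not a stated fact. The 9 to 11 letters are a severe case for one participant, not an effect on the arm.

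Fourth, how a missing AUC point is handled may be set out in the unseen analysis plan. That is fair, and so neither route is assumed here to be the planned one. Non-conversion itself is fixed in the article.

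Last, this is an exploratory analysis in a 60-participant feasibility trial with no single decision threshold, and the error mostly works against the new technique. That limits the consequences but does not remove the distortion in the estimate.

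**Conclusion.** The point holds in a limited form. The rule leaves the worst readings without a value in a listed efficacy outcome. It then either lets a worse eye score better than a less impaired one or conflicts with including all randomised participants. The likely direction is towards the gas arm, so the early difference between arms is understated.

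The size cannot be known from the article. Under the assumptions above it is small to moderate across arms: about 2% to 8% of the AUC difference when 5% to 20% of gas eyes have LP at day 1 and half of these also at week 1. It becomes large only if LP is common and persists. The letter scale under Efficacy outcomes against logMAR in the methods might be read as a contradiction in the analysis. The methods text states and explains the conversion, so only a label needs correcting. The repair is cheap and should be made before the AUC is analysed.

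**What to change.** In the main AUC analysis, give LP and NLP ordered logMAR values (or ranks), each worse than hand motions at 2.3 and with NLP worse than LP. Repeat the analysis over a range of those values and keep the separate report. As a minor edit, state under Efficacy outcomes that the AUC is in logMAR, where higher is worse.

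The cost is about one sentence in the analysis plan and one sensitivity run. The downside is that the assigned values are conventional. This matters little for the planned Mann-Whitney test: in the example eye, every LP value from 2.5 to 3.0 gives a mean logMAR of 0.789 to 0.838, on the correct side of hand motions at 0.769.

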### Methods for additional analyses

Prespecified exploratory subgroup analyses will be performed according to the following variables:

Operation performed; vitrectomy versus combined phacovitrectomy.The choice of whether to perform vitrectomy alone or combined with phacoemulsification will be examined, as the decision to remove the cataract at the same time as surgery may positively affect visual recovery and final acuity. Performing combined cataract surgery may impact on macular hole closure rates with the new technique.Macular hole size: small (≤250 µm), medium (251–400 µm), or large (>400 µm).Anatomic closure is known to be affected by the MLD of the FTMH. Outcomes will be analysed, subgrouped by categorical hole size to determine what effect it has with the novel technique.Lens status; phakic versus pseudophakicVisual outcomes may vary depending on the lens status at the beginning and end of the trial. Emerging or pre-existing cataract, if untreated, may limit BCVA improvement, compared with pseudophakic participants.Surgical learning curve; each surgeon’s first five cases versus subsequent cases.To investigate the role of the surgical learning curve on the outcome of the study, the success of the first five cases of novel gasless surgery that each surgeon performs will be compared against any subsequent cases. This will inform a descriptive analysis of the learning curve for the surgical technique, with an intention to perform a cumulative sum curve if an individual surgeon performs sufficient cases to inform the analysis.Vitreomacular status; vitreomacular traction versus no vitreomacular traction.Primary anatomical closure may be related to the VMT status at the time of surgery. Understanding the impact of VMT may help refine case selection for any subsequent pivotal trial.Duration of macular hole symptoms: Either more or less than the median duration, or more or less than 4 months.FTMH duration is known to influence both primary anatomical success and final BCVA following standard surgery. This subgroup analysis will help determine if this applies to the new surgical approach and help understand the generalisability of the results.

These factors will be applied as effects to the clinical efficacy outcomes.

